**Title:** Protocols for the manuscript “A nutritional biomarker score of the Mediterranean diet and incident type 2 diabetes: integrated analysis of data from the MedLey randomised controlled trial and the EPIC-InterAct case-cohort study”

**Background:** The statistical analysis plan for this study was covered by two protocol documents written prior to establishing a collaboration between the EPIC-InterAct and MedLey studies. These documents are broader in their scope than the current analysis alone, and not all described analyses or named studies are included in the current manuscript.

**Protocol 1** (Pages 2-5 of this document) describes the joint analysis of the MedLey trial and EPIC-InterAct, for which we planned to use a publicly deposited dataset of the MedLey trial (<https://doi.org/10.3390/nu9060534>). The specific dataset did not include most individual fatty acids, but rather groupings of major fatty acids (e.g., sum of saturated fatty acids).

**Protocol 2** (Pages 6-9) describes an initial idea of the EPIC-InterAct investigators to derive nutritional biomarker scores of the Mediterranean diet and other dietary patterns internally based on prediction of self-reported dietary intakes from concentrations of all nutritional biomarkers measured in the cohort. The description of prospective analyses of associations between the biomarker scores and risk of type 2 diabetes was applied to the current analysis.

**Amendments** (Pages 10-11) describe further analytical and data presentation decisions for the current manuscript undertaken upon establishing a collaboration of EPIC-InterAct with the MedLey trial with full biomarker data sharing.

**References** for all documents are available on Page 12.

**Brief description of studies:**

MedLey study is a two-arm parallel randomised controlled trial (RCT) of 137/166 (completed/enrolled) Australians aged ≥ 65 years [1]. Conducting a 6-month intervention, this RCT compared the effect of Mediterranean diet advice and provision of its key foods with the effect of a habitual diet on serum carotenoids, erythrocyte fatty acids and urinary electrolytes. As a measure of compliance to the intervention, self-reported adherence to Mediterranean diet was assessed using a 3-day weighed food diary at months 0, 2 and 4. Biomarkers were measured at months 0, 3 and 6. Raw data were made publicly available at: <https://doi.org/10.3390/nu9060534>.

EPIC-InterAct is a multi-country case-cohort study of type 2 diabetes nested within eight European countries of the European Prospective Investigation into Cancer Study (EPIC) [2]. EPIC-InterAct allows a large-scale epidemiological analysis of approximately twelve thousand incident cases of type 2 diabetes and sixteen thousand participants in the subcohort. Most participants had baseline measurements of plasma carotenoids and phospholipid fatty acids. Habitual diet was assessed using food frequency questionnaires (FFQ) or diet histories.

EPIC-Norfolk, one of the cohorts of EPIC, is a population-based cohort study in East of England [3]. Subsets of participants had baseline and follow-up measurements of plasma carotenoids, plasma phospholipid, and erythrocyte fatty acids, and 24-h and spot urinary sodium and potassium. Habitual diet was assessed at baseline and follow-up using FFQ and 7-day food diary.

**Background:**

Ongoing work in EPIC-InterAct and EPIC-Norfolk aims to derive biomarker scores of habitual adherence to Mediterranean diet using combinations of circulating carotenoids, fatty acids and other nutritional biomarkers. Briefly, cross-validated penalised regression has been modelled to predict Mediterranean diet scores based on nutritional biomarkers. Mediterranean diet scores were calculated based on self-reported diet, using responses to country-specific instruments for dietary assessment. Linear combinations of all available biomarkers were considered, alongside models incorporating first order interactions between biomarkers. Both country-specific and subcohort-wide biomarker scores were developed.

Assessment of external validity of the biomarker scores in a trial setting is desirable. MedLey study dataset includes some of the biomarkers measured in EPIC-InterAct and EPIC-Norfolk which allows for such external validation. The table below shows the overlap between nutritional biomarkers measured in the three studies.

Development of a biomarker of intervention with Mediterranean diet is also of interest. Such a biomarker would have applications in assessment of adherence to the dietary intervention in a clinical setting as well as a non-clinical population-based setting. MedLey trial allows to assess whether or not a specific combination of nutritional biomarkers can differentiate between intervention with Mediterranean diet and habitual diet. The resultant classification model from MedLey trial can be examined for its external validity for a population-based setting by evaluating EPIC-InterAct and EPIC-Norfolk studies.

| **Table** Availability of nutritional biomarker data in MedLey trial and overlap with EPIC-Interact and EPIC-Norfolk studies | | |
| --- | --- | --- |
| MedLey | EPIC-InterAct | EPIC-Norfolk |
|  |  |  |
| **Serum carotenoids** | **Plasma carotenoids** | **Plasma carotenoids** |
| α-carotene, β-carotene, β-cryptoxanthin, lycopene, sum of lutein and zeaxanthin | all available | all available |
|  |  |  |
| **Erythrocyte fatty acids** | **Plasma phospholipid fatty acids** | **Plasma phospholipid and erythrocyte fatty acids** |
| total SFA | sum of individual SFAs | sum of individual SFAs |
| total TFA | sum of individual TFAs | sum of individual TFAs |
| MUFA-n9 | sum of individual MUFA-n9 | sum of individual MUFA-n9 |
| MUFA-n7 | C17:1 | sum of individual MUFA-n7 |
| MUFA-other | sum of remaining MUFAs | sum of remaining MUFAs |
| individual n3 PUFAs: C18:3n3, C20:5n3, C22:5n3, C22:6n3, C20:4n-6 | all available | all available |
| individual n6 PUFAs: C18:2n6, C20:4n6 | all available | all available |
| PUFA n6-other | sum of remaining n6 PUFAs | sum of remaining n6 PUFAs |
|  |  |  |
| **24-h urinary electrolytes** |  |  |
| sodium, potassium, calcium, magnesium | none available | sodium, potassium |

Abbreviations: MUFA – monounsaturated fatty acids; PUFA – polyunsaturated fatty acids; SFA – saturated fatty acids; TFA – trans-fatty acids

Taking advantage of the overlap in measured biomarkers between MedLey trial and EPIC-InterAct, we propose to (i) validate EPIC-InterAct biomarker scores in MedLey trial and (ii) develop a biomarker score of clinical intervention assignment in the trial and evaluate whether it can discriminate between high and low adherence to Mediterranean diet in the cross-sectional setting of EPIC-InterAct.

**Statistical analysis plan:**

**1. Validation of biomarker scores developed in EPIC-InterAct and EPIC-Norfolk studies.**

Derivation of biomarker scores in EPIC-InterAct subcohort and EPIC-Norfolk will be repeated using the reduced set of biomarkers available in MedLey trial. In EPIC-InterAct it will be undertaken in 7 country-specific datasets and one subcohort-wide dataset (pooled dataset of the 7 countries). In each of these 8 datasets, 4 scores will be developed based on combinations of (i) adjusted and unadjusted analysis and (ii) presence or absence of interactions. Overall, 32 biomarker scores will be available. Subcohort-wide biomarker scores will be considered primary outcomes.

Analogous analysis will be undertaken in EPIC-Norfolk, adding further 4 scores. Additionally, we will repeat the analysis in EPIC-Norfolk using the 7-day food diary to estimate the Mediterranean diet score.

Linear mixed effects models will be used to assess the effect of intervention on standardized differences in biomarker scores between the intervention and control group. To reduce the risk of false-positive inference, we will apply false-discovery rate (FDR) correction. We will assume high dependence of different biomarker scores developed within each country or within the whole subcohort. Between-country differences in biomarker scores will be assumed to be driven largely by different data-generating processes. The country of derivation will be considered as a considerably larger source of variation within the pool of all available biomarker scores than the level of adjustment or presence of interactions in the analysis. Thus, FDR correction will be applied separately within groups of biomarker scores defined by the level of adjustment or presence of interactions. Within each of these groups, 9 biomarker scores (7 country-specific and one subcohort wide from EPIC-InterAct, and one from EPIC-Norfolk) will be tested with FDR correction.

Additionally, we will quantify the effects of change in self-reported adherence to Mediterranean diet in MedLey trial (using InterAct scoring cut-offs) on change in biomarker scores. Also, correlations between self-reported adherence and biomarker scores will be calculated cross-sectionally.

**2. Biomarker score of clinical intervention assignment**

This analysis will aim to evaluate whether combinations of nutritional biomarkers can discriminate between the Mediterranean and habitual diet in MedLey trial at 6 months. We will adapt to a binary outcome the methods for evaluation of nutritional biomarkers established in the Women’s Health Initiative feeding trial [4].

Natural-log transformation will be applied to biomarkers to improve normality of distributions. Values outside of 25^th^ percentile minus 3 times the interquartile range (IQR) or 75^th^ percentile plus 3 times the IQR will be removed from the analysis. Logistic regression will be used to develop the biomarker score. Backward selection procedure based on Bayesian information criterion will be used to remove non-informative biomarkers. Multivariable fractional polynomial logistic regression will be used to evaluate the validity of fitting ln-transformed linear terms under log-linearity assumption. Any identified nonlinearities will be included in the logistic regression model. Assumption of no interactions between biomarkers will be evaluated using elastic net logistic regression with first order interactions between biomarkers. Bootstrap-enhanced stability selection will be used to identify consistently selected interactions [5]. Any interactions selected in ≥ 95% of bootstrap samples will be included in the logistic regression model.

Five-fold cross-validated C-statistic will be the primary measure of model performance. We will also calculate net reclassification index and sensitivity and specificity in a clinically relevant scenario.

The analyses will be undertaken using (i) full biomarker data, (ii) excluding urinary calcium and magnesium and (iii) excluding all urinary electrolytes. It will allow to assess the added value of 24-h urine collection to blood-based biomarkers and result in biomarker scores applicable to EPIC-Norfolk (ii) and EPIC-InterAct (iii).

We will test whether the biomarker scores derived in MedLey trial can be used in EPIC-InterAct and EPIC-Norfolk (i) as a measure of degree of adherence to Mediterranean diet and (ii) to discriminate between high and low adherence to Mediterranean diet. The former aim will be addressed by linear regression of the trial-derived biomarker score and Mediterranean diet score based on dietary self-report. High and low adherence ranges will be defined by using the statistics in MedLey trial. To define the high adherence, we will use the median of the Mediterranean diet score +/- 1 point in the intervention group of MedLey trial. To define the low adherence, we will use the corresponding median +/- 1 point in the habitual diet group. Logistic regression and c-statistic will be used to evaluate discrimination between the two groups in EPIC studies. Net reclassification improvement will be estimated by analysing a predictive capability of the biomarker score in comparison to an intercept-only model and a multivariable-adjusted model including variables readily available in a clinical setting (age, sex, recruitment sites, and smoking status).

We will consider analysing prospective associations between the biomarker scores and type 2 diabetes (EPIC-InterAct) and cardiovascular endpoints (EPIC-Norfolk).

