**Amendments (summarised on 18/11/2022):**

1. *Use of raw data of individual fatty acids rather than publicly deposited data of groups of fatty acids*. Following gaining access to full biomarker data in the MedLey trial, EPIC-InterAct investigators reconsidered the “biomarker score of clinical intervention assignment” (Protocol 1) as our primary approach to derivation of a biomarker score of the Mediterranean diet, as reported in the current manuscript. Prior to this, we viewed the use of groupings of fatty acids in the MedLey trial (as available in the publicly deposited dataset) for external application of the biomarker score to EPIC-InterAct as too strong a threat to validity of the analysis to consider this type of biomarker score as our primary approach, because the composition of individual fatty acids within such groupings may have been fundamentally different between the two studies.

2. *Use of logistic elastic-net regression modelling individual biomarkers and their first-order interactions rather than use of standard logistic regression with backwards selection of individual biomarkers*. We increasingly recognised the utility of elastic net regression to develop a model predicting a dependent variable with multiple correlated predictors. We also found the assumption of no interactions between biomarkers in the score to be severely violated and we allowed for selection of predictors among all pairwise biomarker interactions in addition to log-linear terms. Because of the need to consider a pool of predictor variables exceeding the number of participants following this amendment, we applied logistic elastic net regression as our primary method of variable selection in lieu of logistic regression with backwards selection based on minimising the Bayesian information criterion.

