3. *Method of variable selection stabilisation.* In the logistic elastic net regression analysis, we exchanged the bootstrap-enhanced stability selection of biomarkers for stability selection with repeated cross-validation. We selected the former a priori based on our earlier experience of observational derivation of biomarker scores using linear models (Protocol 2). It did not identify any biomarker terms consistently predictive of randomised assignment in the MedLey trial despite selection of multiple biomarker terms in individual runs of elastic net regression models. Upon additional reading of the literature, we found that bootstrapping for classification problems is suboptimal and favours overly parsimonious models [15]. This issue would be reasonably expected to be exacerbated by performing variable stability selection across bootstrap samples, which is consistent with our lack of identification of biomarker predictors using the bootstrap-based stability selection approach.

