4. *Omission of secondary analyses*. We considered several secondary analyses as being of little benefit for our inference and our final report and omitted them: 1) computation of net re-classification index in the MedLey trial; 2) computation of relevant reclassification indices in the EPIC-InterAct; 3) assessment of utility of the biomarker score over and above established risk factors for prediction of type 2 diabetes; and 4) longitudinal analyses for incident outcomes in the EPIC-Norfolk study. 1) In the MedLey trial, C-statistic was considered as satisfactory to evaluate the performance of the derived biomarker scores. 2) In EPIC-InterAct, “validation” of the biomarker score was considered invalid to assess by using self-reported dietary indices as the reference measure because of the measurement error in subjective reporting and potentially limited construct validity of the Mediterranean diet score. 3) To make the manuscript succinct and focused on the single research aim, we decided not to explore whether inclusion of the nutritional biomarkers would merit prediction of type 2 diabetes risk currently available in a clinical setting. Lastly, 4) the EPIC-Norfolk study is a part of EPIC-InterAct, ascertaining the incidence of a number of disease endpoints, not only type 2 diabetes (n diabetes cases = 681). For the purpose of simplicity and clear focus on type 2 diabetes as the primary outcome in the EPIC-InterAct (n cases = 9,453 in the current study), we decided to reserve any longitudinal analyses for multiple outcomes in the EPIC-Norfolk Study for future publications.

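### The plan does not require term selection and tuning to be repeated inside the cross-validation folds; carried out in its written order, the primary C-statistic is optimistic

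*Combined protocol and SAP*

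**What the plan says.** Protocol 1, section 2 of the statistical analysis plan, builds one logistic model for randomised diet at 6 months. Biomarkers are removed backwards by BIC, non-linear terms found by fractional polynomials are added, and interactions that meet a 95% bootstrap selection threshold are added. The next paragraph says: "Five-fold cross-validated C-statistic will be the primary measure of model performance". Sensitivity, specificity and a net reclassification index are also planned. The work is done for three biomarker sets: all markers, without urinary calcium and magnesium, and without urine.

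The amendments of 18/11/2022 change the selector. Item 2 adopts a logistic elastic net on single markers and all pairwise products, citing "the need to consider a pool of predictor variables exceeding the number of participants". Item 3 reports: "we exchanged the bootstrap-enhanced stability selection of biomarkers for stability selection with repeated cross-validation". Item 4 drops the reclassification index in the trial because the "C-statistic was considered as satisfactory to evaluate the performance of the derived biomarker scores".

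None of these sections says whether selection and tuning run once on the whole sample or again in each training fold. Protocol 2, by contrast, does separate development from testing for other models. Its score derivation leaves out one centre or country at a time, and its predictive modelling develops in seven countries and validates in the eighth.

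**The concern.** Cross-validation gives an honest C-statistic only if the held-out participants played no part in any step that used the outcome. Here the outcome is the randomised arm. If terms are chosen with all arm labels and only the coefficients are re-estimated in each fold, the held-out fold is not independent of the model that it tests. The problem grows with the number of candidate terms, and the amendments raise that number above the sample size.

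At stake is the primary measure of how well the score separates the two assigned diets. The comparisons in the EPIC studies use self-reported adherence as the reference. Item 4 of the amendments itself regards that reference as unsuitable for validation, although the analysis was later added at peer review. Those comparisons therefore do not replace an unbiased trial C-statistic.

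**Working it through.** The documents give no C-statistic, sample-size or power figure for this analysis, so there is nothing of the plan's own to reproduce. The check has two parts.

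**1. Size of the candidate pool.** The inputs come from Protocol 1. MedLey had "137/166 (completed/enrolled) Australians aged ≥ 65 years", so n = 137. The biomarker table lists 5 carotenoids ("α-carotene, β-carotene, β-cryptoxanthin, lycopene, sum of lutein and zeaxanthin"). It also lists 12 fatty-acid variables: SFA, TFA, three MUFA groups, four n-3, two n-6 and other n-6, with C20:4n6 counted once although it appears in two rows. That makes 17 blood markers, and the 4 urinary electrolytes bring the total to 21.

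Single terms plus all pairs = k + k(k − 1)/2.

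- k = 16: 16 + 120 = 136
- k = 17: 17 + 136 = 153
- k = 21: 21 + 210 = 231

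Both 153 and 231 exceed 137, which agrees with item 2 of the amendments. The number of individual fatty acids available after item 1 is not given, so 153 is an illustration based on the public dataset.

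**2. Effect of where selection is done.** Simulated trials had n = 137, equal arms (the allocation ratio is not given), normal markers with pairwise correlation 0.3, and four markers shifted by 0, 0.3, 0.6 or 1.0 SD. All of these except n are assumptions. Three C-statistics were compared: (a) terms selected on all 137, then five-fold cross-validation of the refitted model; (b) selection repeated in each training fold; (c) the selected model applied to 2,000 new subjects. Optimism is a − c.

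The BIC selector used linear terms only, with 150 runs per setting. The elastic net used mixing 0.5, three repeats of cross-validation, a 50% selection threshold and a ridge refit (all assumed), with 34 to 40 runs per setting.

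| Selector | Shift (SD) | (a) Selected once | (b) In each fold | (c) New subjects | a − c |
|---|---|---|---|---|---|
| BIC, 17 markers | 0 | 0.559 | 0.508 | 0.501 | 0.058 |
| | 0.3 | 0.640 | 0.556 | 0.563 | 0.077 |
| | 0.6 | 0.790 | 0.709 | 0.728 | 0.062 |
| | 1.0 | 0.917 | 0.869 | 0.881 | 0.036 |
| BIC, 21 markers | 0 | 0.543 | 0.494 | 0.500 | 0.043 |
| | 0.3 | 0.646 | 0.560 | 0.568 | 0.078 |
| | 0.6 | 0.802 | 0.718 | 0.733 | 0.069 |
| | 1.0 | 0.927 | 0.876 | 0.886 | 0.041 |
| Elastic net, 153 terms | 0 | 0.614 | 0.493 | 0.499 | 0.115 |
| | 0.3 | 0.649 | 0.515 | 0.532 | 0.117 |
| | 0.6 | 0.828 | 0.653 | 0.694 | 0.134 |
| | 1.0 | 0.947 | 0.836 | 0.863 | 0.084 |

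The largest Monte Carlo standard error is 0.007 for BIC and 0.020 for the elastic net. A shorter elastic-net run with another seed (15 to 18 replicates) gave differences of 0.08 to 0.14. Selection in each fold came within about 0.02 of new-subject performance for BIC and about 0.04 for the elastic net, usually slightly below it.

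**The case against.** The strongest reply is that no sentence says selection was done once on the whole sample. Section 2 lists modelling steps and then a performance measure, and paragraph order is not an algorithm. Stability selection by repeated cross-validation can be run wholly inside an outer training set. The manuscript's methods, which are not among the documents, may state this. That stands: whole-sample selection is the natural reading but not a documented fact. Silence on nesting does not dispose of the point, because the plan as written permits the biased procedure.

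A reader might also infer more than the documents support:

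- **Optimism of 0.2 or more.** Forcing the best 5 to 10 noise terms into the model gives a cross-validated C of 0.71 to 0.76. However, neither Protocol 1 nor the amendments use such a selector. Similarly large gaps arise with an elastic net that lacks the stability selection of item 3.
- **The C-statistic is the only performance measure left in the trial.** Item 4 drops only the reclassification index there. Sensitivity and specificity are not listed as omitted.
- **The C-statistic decides whether the score goes to EPIC-InterAct.** No section makes it a gate. Item 1 attributes the choice of this score as primary to access to individual fatty-acid data.
- **The diabetes result is inflated.** That association is estimated in separate participants (9,453 cases), so optimism in the trial C-statistic does not carry over directly.

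**Conclusion.** The concern holds in conditional form. The plan does not require selection and tuning inside the folds, and carried out in its written order it yields an optimistic primary C-statistic. Illustratively, the excess over new subjects is about 0.04 to 0.08 for BIC backward selection and 0.08 to 0.13 for the amended selector. With no effect at all, the reported value would be about 0.56 (BIC, 17 markers) to 0.61 (elastic net).

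These figures rest on the assumed correlation, signal, marker count and tuning rule, none of which the documents give. They are not estimates of the trial's own bias. The direction was the same in every setting examined.

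A second source of optimism is documented and separate. Items 2 and 3 record that interactions were admitted after the no-interaction assumption was found to fail, and that the stabilisation method was changed after the planned one identified no consistent terms in MedLey. Nesting the final selector does not remove the effect of those choices.

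**What to change.** In Protocol 1, section 2, replace the sentence on the C-statistic with: *All outcome-dependent steps (penalty tuning, stability selection, choice of non-linear and interaction terms, final fit) are repeated inside each training set of a repeated outer five-fold cross-validation, and the primary C-statistic, with a confidence interval, is calculated on held-out participants only.*

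Apply the same procedure to all three biomarker sets and to sensitivity and specificity. Steps that do not use the arm, such as the interquartile-range rule for outliers, are not the source of this bias. Running the same pipeline on permuted arm labels would give a useful null distribution but is optional.

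Alongside the C-statistic, state that interactions were admitted and the stabilisation method changed after trial results were seen, and that nesting does not correct for this.

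If selection was already nested, one sentence saying so settles the main point. If not, the cost is a rerun on existing data, more computing time and a lower reported C-statistic. No new data are needed.
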